## **5. TREATMENT OF SUBJECTS**

### **5.5 Investigational product/treatment**

The intervention group will start complementary feeding at the corrected age of 12 weeks, when gross motor development should enable safe eating. The control group will start complementary feeding at the corrected age of 17 weeks. The pattern and structure of the complementary feeding will be according to the advice of the well baby clinics in the Netherlands, using a standardized nutrition schedule.

The parents will receive information direct after the randomization about the group allocation. One week before they are assigned to start with complementary feeding, they will receive a reminder by phone. If this is not possible an email or a letter by post will be send. Parents will have one week to start with complementary feeding, either at the corrected age of 12 weeks or at the corrected age of 17 weeks. Parents will receive detailed information about complementary feeding, what kind of food to start with, how often they have to give solid foods, and some recipes. The introduction of complementary feeding is divided in 4 steps: 1) introduction of vegetables, 2) introduction of fruits, 3) introduction of cereal, and 4) introduction of a warm meal. Parents receive information when to move on to the next step. The well baby clinics and attending pediatricians are informed about the group allocation and are asked to support parents to start with complementary feeding by the time they are allocated. They also receive the information that the parents received regarding how to start with complementary feeding. In case there is a reason not starting complementary feeding at the time of allocation, parents are asked to report this and the reason why not starting in the diaries. Furthermore, the diaries will point out at what time the parents started with complementary feeding.

For the term born children (control group B) there will be no intervention with complementary feeding.

### **5.6 Use of co-intervention (if applicable)**

The use of co-medication is allowed in all patients.

---

**5.7 Escape medication (if applicable)**

Not applicable

**6. INVESTIGATIONAL PRODUCT**

Not applicable.

**6.1 Name and description of investigational product(s)****6.2 Summary of findings from non-clinical studies**

*<One may refer to the Investigator's Brochure (IB), Investigational Medicinal Product Dossier (IMPD), Summary of Product Characteristics (SPC) or a similar document (if applicable), by mentioning the relevant pages in that document. Be sure that the information is up to date and references to peer reviewed papers in (biomedical/scientific) journals should be given where appropriate.>*

**6.3 Summary of findings from clinical studies**

*<See explanatory text of chapter 6.2, including remark>*

**6.4 Summary of known and potential risks and benefits**

*<See explanatory text of chapter 6.2, including remark>*

**6.5 Description and justification of route of administration and dosage****6.6 Dosages, dosage modifications and method of administration****6.7 Preparation and labelling of Investigational Medicinal Product****6.8 Drug accountability**

*<Please describe the procedures for the shipment, receipt, disposition, return and destruction of the investigational medicinal products.>*

**7. NON-INVESTIGATIONAL PRODUCT**

Not applicable, see chapters 7.1; 7.6; and 7.7.

*<This chapter is applicable for any other product that is used in the study, like challenge agents or products used to assess end-points in the trial. This can be a medicinal product or a food product or a chemical compound or stable isotope or other product.  
This chapter does **not** include co-medication or escape medication, these are already mentioned in chapter 5*

*For products to be used as in usual clinical practice the information can be limited to the chapters 7.1, 7.6 and 7.7 >*

### **7.1 Name and description of non-investigational product(s)**

### **7.2 Summary of findings from non-clinical studies**

*<One may refer to the Investigator's Brochure (IB), Investigational Medicinal Product Dossier (IMPD), Summary of Product Characteristics (SPC) or a similar document (if applicable), by mentioning the relevant pages in that document. Be sure that the information is up to date and references to peer reviewed papers in (biomedical/scientific) journals should be given where appropriate.>*

### **7.3 Summary of findings from clinical studies**

*<See explanatory text of chapter 7.2, including remark>*

### **7.4 Summary of known and potential risks and benefits**

*<See explanatory text of chapter 7.2, including remark>*

### **7.5 Description and justification of route of administration and dosage**

### **7.6 Dosages, dosage modifications and method of administration**

### **7.7 Preparation and labelling of Non Investigational Medicinal Product**

### **7.8 Drug accountability**

*<Please describe the procedures for the shipment, receipt, disposition, return and destruction of the non-investigational medicinal products.>*

---

## 8. METHODS

### 8.1 Study parameters/endpoints

#### 8.1.1 Main study parameter/endpoint

The main study parameter of this study is the prevalence of obesity determined by measuring the BMI at the corrected age of 2 years, according to the IOTF cut-off value. In addition, BMI will also be determined before the start of complementary feeding and at the corrected age of 1 year. A variation of 6 weeks before and after the corrected age of 1 and 2 years will be accepted.

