## SUMMARY

**Rationale:** optimal timing of introduction of complementary feeding during infancy is necessary for both nutritional and developmental reasons. Limited evidence is available about the optimal age of solid food introduction in preterm infants and implications for both short and long term health.

**Objective:** to analyze the effect of early (12 weeks corrected age) versus late (17 weeks corrected age) introduction of complementary feeding on obesity at the age of 2 years in preterm infants.

**Study design:** the study comprises a randomized parallel group open-label controlled intervention study in which premature born children will be randomized to receive complementary feeding at the corrected age of 12 weeks or at the corrected age of 17 weeks.

**Study population:** preterm infants born between 30 and 35  $\frac{6}{7}$  weeks gestational age.

**Intervention:** the intervention group will start complementary feeding at 12 weeks corrected age. The control group will start complementary feeding at the corrected age of 17 weeks. The pattern and structure of the complementary feeding will be according to the advice of the well baby clinics in the Netherlands.

**Main study parameter/endpoint:** the main study parameter is the prevalence of obesity at the age of 2 years determined by BMI-score, according to the IOTF cut-off values and will be interpreted as association.

**Nature and extent of the burden and risks associated with participation, benefit and group relatedness:** the risks associated with this study are minimal. There will be no benefit for the individual participating in this study. To determine correlations between height, weight, BMI, and eating behaviour in preterm infants it is important to perform this study in this age category.

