## 2. OBJECTIVES

Main objective:

The main objective of this study is to analyze the effect of early (12 weeks corrected age) versus late (17 weeks corrected age) introduction of complementary food (weaning) on the prevalence of obesity at the age of 2 years in preterm infants. Overweight (including obesity) is determined by measuring the BMI, according to the IOTF cut-off values. Preterm infants are included when born between 30 and 35/7 weeks of gestational age.

The difference in weeks between the early and late group seems to be small. Palmer et al recommended that 13 weeks is considered as an appropriate age to start with complementary feeding and King suggested the infants should be at least 3 months corrected age, meaning 12 weeks (see table 1). For this reason, the early intervention group will start with complementary feeding at 12 weeks corrected age. However, starting with complementary feeding at 17 weeks corrected age in a child born at 30 weeks gestational age means that the uncorrected age or postpartum age is 27 weeks. Starting with complementary feeding at the uncorrected age of 27 weeks corresponds with approximately 6.2 months (see table 1). This is the latest acceptable time to start with complementary feeding, since research has proven that at about 6 months the volume of ingested human milk by exclusively breast-fed infants becomes insufficient to meet the requirements of energy, protein, iron, zinc, calcium, selenium and some fat-soluble vitamins (A and D). In conclusion, these considerations led to the early group (12 weeks corrected age) and late group (17 weeks corrected age) to start with complementary feeding.

| GA                             | Corrected age          | Postpartum age  |
|--------------------------------|------------------------|-----------------|
| 30                             | Early: 12 weeks        | 22 weeks        |
| 35  / 7 | Late: 17 weeks         | 21 weeks        |
| 30                             | Late: 17 weeks         | 27 weeks |
| 35  / 7 | Early: 12 weeks | 16 weeks        |

**Table 1:** Showing the post-partum age of the intervention groups. GA = gestational age. In bold: 12 weeks is corresponding with 3 months corrected age, 27 weeks is corresponding with 6.2 months uncorrected age (= postpartum age).

Sub-objectives are:

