### 4.3 Sample size calculation

The sample size calculation for this study is based on previous reported effects. In a population based study Jingxiong et al reported that introduction of complementary feeding before the age of 4 months resulted in a 76% higher odds in developing overweight than children introduced to complementary feeding after 4 months. Overweight in this study was defined as weight-for-length/height  $\geq 2$ SD above the median of the WHO reference for sex, i.e. weight-for-length/height z-score  $\geq 2$ SD. A study by Young et al reported that excess weight gain (defined as gaining  $\geq 0.5$  in weight-for-age Z-score) between 4 to 6 months was associated with an odds ratio of 2.5 for overweight at 18-24 months. This led to the conclusion that rapid early weight gain, for example due to early weaning, could result in obesity since known post-natal risk factors for obesity are rapid early weight gain and early weaning. Based on these studies we expect that the introduction of early complementary feeding in children will result in a higher prevalence of overweight children at the age of 2 year in comparison to later introduction of complementary feeding. Based on the given odds ratio of 1.76 and 2.5 an odds ratio of 2.3 was used to calculate our sample size. In 2009, the prevalence of overweight was 8% in two year old children in the Netherlands. Overweight was determined by measuring the BMI. BMI was calculated as weight/height and expressed as kg/m^2. Overweight and obesity prevalence rates were calculated using International Obesity Task Force (IOTF) cut-of values. In this study, the same calculation and definition will be used. Information of the prevalence of overweight in premature infants is lacking. Bocca-Tjeertes et al has shown that preterm infants are a growth restraint compared to term infants. On the other hand, Euser et al found a greater fat mass normalized for weight in preterm infants. Given this contrasting information on preterm infants, a slightly lower prevalence of overweight of 6% was used to calculate the sample size. Using the odds ratio of 2.3, the intervention group will have a prevalence of overweight of 13%. With a 0.05 significance level and a power of 80% a minimal sample size of 275 patients per group is required to detect a significant increase in the prevalence of overweight. Loss to follow-up is

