### 8.3.3 Body Mass Index (BMI) – Standard care

BMI will be calculated by the following formula.  $BMI = \text{Weight (kg)} / \text{height (m)}^2$ . The Standard Deviation Score (SDS) of the Dutch growth standards will be calculated.

Overweight and obesity at the age of 2 year will be determined using the IOTF criteria. The participants will be compared to the Dutch population.

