## 10. STATISTICAL ANALYSIS

Since the sample size was not archived, the data will be interpreted with caution. Data will be analyzed on an intention to treat basis. In addition, we will also perform a per protocol analysis, taking into account the attrition rate. In case of missing values we will use multiple imputation. For the per protocol analysis, the criteria for the start of complementary feeding will be 12-13 weeks for the early group and 16-17 weeks for the late group. A p-value of 5% will be regarded as statistically significant and results will be presented with 95% confidence intervals.

Categorical data will be presented in absolute numbers and percentages. If a metric variable is normally distributed results will be shown in mean and standard deviation (sd). If a metric variable is not normally distributed median will be used with the interquartile range.

Descriptive data on BMI will be compared with the most recent Dutch growth chart. For the primary study parameter, the prevalence of obesity, the percentage of patients that develop overweight by using the IOTF will be calculated and intervention group and control will be compared including prevalence ratios with 95% confidence intervals. Furthermore, BMI and BMI z-scores between the intervention and control group will be compared as continuous variables.

The results of the questionnaires (BEBQ, CFQ, ITQoL / PedsQL, ASQ) will be analysed according to the scoring tables attached to the questionnaires. Allergy will be scored by a SCORAD form and can be presented as continuous or categorical variable. All blood and faeces results will be analysed as continuous or categorical variable. The diary results will be analysed as a continuous variable.

For all sub-objectives (as formulated in chapter 2), the intervention group and control group will be compared to determine the effect of early versus late introduction of complementary food, using a independent t-test or nonparametric test. For subgroup analysis, i.e. for children with respiratory problems or tube feeding, logistic regression will be used.

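### The primary endpoint is named as obesity, but the sample size and the counting rule use overweight; the stated 80% power belongs to overweight

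*Protocol*

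**What the plan says.** Obesity is named as the primary outcome in these places:

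- Summary: "the main study parameter is the prevalence of obesity at the age of 2 years determined by BMI-score".
- The last sentence of Section 1.1.3 and the first sentence of the main objective in Section 2, both of which refer to the prevalence of obesity at two years.
- Section 8.1.1: "The main study parameter of this study is the prevalence of obesity determined by measuring the BMI at the corrected age of 2 years", judged against a single IOTF cut-off value.

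Overweight is what is defined, sized or counted in these places:

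- Section 2, directly after the obesity objective: "Overweight (including obesity) is determined by measuring the BMI, according to the IOTF cut-off values".
- Section 4.3, which takes 6% overweight in the control arm and continues: "Using the odds ratio of 2.3, the intervention group will have a prevalence of overweight of 13" per cent. It then says: "With a 0.05 significance level and a power of 80% a minimal sample size of 275 patients per group is required". It also adopts for this trial the IOTF-based overweight definition of the Dutch survey that supplied the 8% reference rate.
- Section 10, which holds both terms in one sentence: "For the primary study parameter, the prevalence of obesity, the percentage of patients that develop overweight by using the IOTF will be calculated".

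Section 8.3.3 treats the two as separate categories: "Overweight and obesity at the age of 2 year will be determined using the IOTF criteria".

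**The concern.** Section 2 speaks of overweight as including obesity, so obesity is the narrower category and its rate cannot exceed that of overweight. The two terms are therefore different binary outcomes with different event counts, not synonyms. A reader of the Summary or Section 8.1.1 would take obesity to be tested. A reader of Section 4.3 would take it to be overweight. Section 10, which should settle the matter, uses one word as the label and the other for the count.

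Two things are at stake. A primary binary endpoint needs one threshold, because the p-value, the prevalence ratio and its interval all depend on it. And the 80% power is a statement about overweight; placed beside an endpoint called obesity, it promises something the calculation never addressed. This is not a detail that a protocol leaves to its statistical analysis plan: the protocol sets the endpoint itself, in two ways.

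**Working it through.** **Inputs from the protocol.** Section 4.3: control rate 6%, odds ratio 2.3, intervention rate 13%, significance level 0.05, power 80%, 275 per group. The 5% loss and the totals of 579 and 600 follow at the end of the same section. Section 8.2: allocation 1:1. Sidedness is not stated; two-sided is used because it reproduces the result (one-sided would give 216 per group).

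**Step 1. Intervention rate.** Odds at 6% are 0.06/0.94 = 0.0638. Multiplied by 2.3 this is 0.1468, and 0.1468/1.1468 = 12.8%, which the protocol rounds to 13%.

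**Step 2. The plan's sample size.** Two proportions, pooled variance under the null, no continuity correction, with p̄ = 0.095:

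n = [1.96·√(2·0.095·0.905) + 0.8416·√(0.06·0.94 + 0.13·0.87)]² / 0.07²
= (0.8127 + 0.3465)² / 0.0049 = 274.2, so **275 per group**.

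Allowing for loss: 550/0.95 = 578.9, so **579**. Both figures match Section 4.3. Power at 275 per arm for 6% against 13% is 80.1%. With the unrounded 12.8%, 275 per arm gives 78.2% and 288 would be needed; this is minor and does not affect the point.

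**Step 3. The same size applied to obesity alone.** The protocol gives no obesity rate, so the control rates below are assumptions, shown as a range. The odds ratio stays at the protocol's 2.3, although that value was chosen for overweight. The formula is

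power = Φ{ [d·√n − 1.96·√(2p̄(1−p̄))] / √(p₁(1−p₁) + p₂(1−p₂)) }, with d = p₂ − p₁ and n = 275.

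Worked case, 1% control rate: p₂ = 2.27%, d = 0.0127, p̄ = 0.01635. The numerator is 0.2107 − 0.3515 = −0.1409, the denominator is 0.1791, the ratio is −0.786, and power is 22%.

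| Assumed control rate | Early-arm rate at OR 2.3 | Power at 275 per arm | Per arm for 80% |
|---|---|---|---|
| 0.5% | 1.1% | 13% | 3,096 |
| 1% | 2.3% | 22% | 1,564 |
| 2% | 4.5% | 38% | 798 |
| 3% | 6.6% | 51% | 543 |
| 4% | 8.7% | 63% | 415 |

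At 1% to 2%, the control arm would yield about 3 to 6 events (275 × 0.01 = 2.75; 275 × 0.02 = 5.5). With so few events the normal approximation is rough. Exact calculation gives 20% (chi-square) or 12% (Fisher) at 1%, and 38% or 29% at 2%.

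**Step 4. Effect needed for 80% on obesity at 275 per arm.** The odds ratio would have to be about 8.4, 5.3, 3.7 or 3.0 at control rates of 0.5%, 1%, 2% or 3%.

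**The case against.** The strongest reply is that overweight is plainly what is meant. Section 2 defines overweight including obesity straight after the objective, Section 4.3 adopts the overweight definition for this trial, and the only sentence in Section 10 that says how the primary parameter is computed counts overweight. No section describes a primary analysis of obesity alone. This stands, and it decides which way the wording should be corrected. It does not remove the contradiction, because Section 8.1.1 and the Summary still name the other outcome and Section 10 still carries its label.

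A second reply is that the low power in the table rests on an odds ratio borrowed from overweight. This also stands. Section 1.1.2 cites a sixfold rise in obesity risk by age three. Taken as an odds ratio of 6, 275 per arm would give about 87% power at a 1% control rate and 99% at 2%, though 59% at 0.5%. The sizing does not use that figure, but the table holds only under the protocol's 2.3.

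Third, Section 10 says that the planned sample size was not reached, so 80% no longer describes the trial under either threshold. That is correct; the figures above concern the planned size.

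A reader might also infer that unblinded investigators are free to pick the threshold after seeing the data. Allocation is open (Section 8.2) and both categories come from the same BMI, but Section 10 does state which children are counted. The documents show loose labelling, not an open choice.

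**Conclusion.** The protocol contradicts itself on the primary threshold, and its 80% power applies to overweight including obesity. That much needs no assumption: the wording is on the page, and 275 and 579 reproduce from the overweight rates.

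The size of the power loss is conditional. With an odds ratio of 2.3, assumed obesity rates of 0.5% to 4% in the late arm and 275 children per arm, power for obesity alone would be about 13% to 63%.

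Two stronger conclusions are not supported. A reader might infer that the trial's primary test will be on obesity and is therefore severely underpowered. The counting rule in Section 10 points to overweight, and a much larger effect on obesity would change the power. A reader might also infer that the registered endpoint differs from the one tested. The protocol mentions registration but does not reproduce the entry, so nothing can be said about it.

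**What to change.** In the Summary, the closing sentence of Section 1.1.3, the main objective in Section 2, Section 8.1.1 and the primary-parameter sentence in Section 10, replace the prevalence of obesity with: *prevalence of overweight including obesity (IOTF overweight cut-off) at 2 years corrected age*. This agrees with the definition in Section 2, the sizing in Section 4.3 and the count in Section 10. Add one sentence to Section 10 making clear that any analysis of obesity alone is not the primary test and is not covered by the stated power.

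The cost is a wording amendment. No new data, measurement or sample size calculation is needed. It should be made before the arms are compared on either threshold.

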#### 8.1.2 Secondary study parameters/endpoints

The secondary study parameters:

- Eating behavior of the child by using and tolerating complementary feeding, by using the BEBQ and CFQ.
- Health Related Quality of life by using the ITQoL of or Pediatric Quality of Life Inventory (PedsQL).
- Development by using the Ages and Stages Questionnaire (ASQ)
- Allergies, by using the SCORAD.
- Microbiota of faeces

#### 8.1.3 Other study parameters (if applicable)

Other study parameters are age, gender, height, weight status, family history, allergy/atopy status, education, social economic status, and ethnicity of the parents. Maternal information regarding the pregnancy, parity and delivery are collected as well, including maternal illness during pregnancy, such as maternal diabetes mellitus, hypertensive disorders during pregnancy, and thyroid disease. This parameters will be obtained via digital questionnaires or child records. Information on perinatal and early life factors, such as APGAR-score, birth weight, reason for prematurity, respiratory support, blood transfusion, antibiotics use, NICU admission, type of feeding until complementary feeding is started, and illness are prospectively collected. Furthermore, information on sickness and medical check-ups.

